## Methods/design

### Study design and randomization

This multi-centre study in the Netherlands has an unblinded stepped wedge cluster randomized design [32] with pre- (T0) and post-intervention measures after six months (T1), with a follow up after twelve months (T2). The framework of this trial is superiority, whereby we will compare the outcomes between the control and intervention group, and between baseline and follow up data. Seven departments of five University Medical Centres will participate in the study, four kidney transplantation units, one heart transplantation unit, one liver transplantation unit and one lung transplantation unit. The coordinating centre is Erasmus MC, department Nephrology and Transplantation. This department is responsible for coordinating the study, distributing the questionnaires, training of the NPs and the data analysis. A steering committee is present to contribute ideas and to oversee the process.

Given the nature of the programme and the fact that NPs are trained in delivery of the intervention and communication skills, the NPs delivering the intervention cannot be blinded to the group allocation. Therefore, randomization will be performed at the department level. This will be carried out by an independent professional not involved in the study using sealed opaque envelopes. The envelopes with department names and envelopes with start date will be prepared and shuffled by the researcher. The independent professional then randomly chooses the envelopes. All seven participating departments commence the study with standard care i.e. the control period (see Fig. 1) in September 2020. The timing of transition of departments from control to experimental  period is randomized. The first department will be randomized to commence the experimental period in March 2021. During the experimental period, patients receive standard care plus the ZENN intervention. Patients in the control period are different from the experimental period patients, meaning that they will not cross-over.

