**Fig. 1 Fig1:**
[figure not shown]
Flowchart of the study

In the month prior to the initiation of the experimental period for each department, the NPs will be trained in the delivery of the intervention. At this point in time, there will still be patients in the control period who are yet to complete the follow-up measure. During this month they may receive care in the form of a standard consultation from this NP. Therefore, there is potential for ‘contamination’ of these control period patients in the sense that their NPs will have already received the training associated with the intervention. To limit the risk of contamination, the following strategies will be put in place: standard care protocol will be used in all consultations for control period patients, and the questionnaires will not be administered by the NP but will be sent out by the researcher.

The ZENN intervention will be conducted in the outpatient clinic of each participating department. Due to the COVID-19 pandemic, the possibility of carrying out the intervention through tele-medicine is being examined. For the schematic overview of the inclusion, see Fig. 1. To enhance the validity of the study, the Standard Protocol Items: Recommendations for Interventional Trials (SPIRIT) guidelines [33] will be followed.

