### Data analysis

Data will be coded with a unique code per patient. The key of these codes will be safeguarded by the coordinating and the principal investigator with a password. No other persons will have access to the key. All data will be kept for 15 years, according to the Dutch Personal Data Protection law. Data will be stored using the data capture applications Gemstracker and Limesurvey. These systems are managed by the Department of Information Management of Erasmus MC and are secured with an individual password for the coordinating and principal investigator.

To assess if randomization has resulted in comparable groups, we will compare patients in the control and in the experimental period at baseline (T0) on characteristics as well as primary and secondary outcomes. Descriptive statistics will be presented as frequencies (%) for categorical variables. Continuous variables will be described as median and interquartile range for non-normally distributed variables and as mean and standard deviation for normally distributed data.

The primary analysis of the study is an initial univariate exploration of the effect of the intervention. Continuous outcomes at T1 between the patients in the control and experimental period will be compared and tested using the Mann-Whitney *U* test for non-normally distributed data and the independent-samples *t* test for normally distributed data. For the BAASIS, a 2 × 2 chi-squared test will be conducted (adherent yes/no × control/experimental group). In univariate analyses, the relationship between patient characteristics (such as age and gender) and medical characteristics (such as organ type and centre) and the outcomes will be assessed.

For the multivariate analyses, linear mixed models analysis will be conducted to account for repeated measures per patient, covariates organ and transplant centre and other significant covariates. All models will be estimated using intention-to-treat analysis incorporating all eligible patients from whom data was obtained. There are three measurement time points (T0, T1 and T2) to be included in these analyses. For missing data in predictor variables, we will use multiple imputation. A *p* value < 0.05 is considered statistically significant.

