We will assess the differences on the primary and secondary outcomes between patients in the control period and versus the experimental period at both T1 and T2 on the outcomes (between-groups comparison). We will also assess the differences on the outcomes between T0–T1 and T0–T2 within the control period and within the experimental period (within-groups comparison). The secondary outcome measure *medication adherence*, which is a dichotomous variable, will be analysed with a generalized estimating equations logistic regression. If the effect of the intervention is found to differ according to organ type then separate explorative multivariate analyses will be conducted to assess the effect per organ.

Among NPs, in an initial univariate analysis, we will compare self-management support skills, using all scales of the SEPSS-36, before and after the experimental period (T0-prior to training and T1-at the end of the implementation period). For non-normally distributed data, we will use the Wilcoxon signed-rank test and the paired samples *t* test in case of normally distributed data.

The video recordings of the NPs will be assessed in blocks of 5 minutes each. Of every recording, a 5-minute clip will be randomly assigned to be observed by two researchers independently. The clips from the control period will be compared with the clips of the experimental period on the needs-thwarting and needs-supporting subscales and tested using the Wilcoxon-signed rank test for non-normally distributed data and the paired samples t-test in case of normally distributed data.

The interviews and qualitative questions in the questionnaire, which will be used to qualitatively evaluate the intervention and the nurse-led care, will be transcribed by at least two researchers independently and analysed thematically [55] using NVivo.

To examine if contamination occurred, we will compare the primary outcome (Skills and Technique Acquisition - heiQ) among control period patients in the contamination phase versus those in the control period not in the contamination phase at T1 and T2. This will be done using an independent samples *t* test. If there is a significant difference, we will control for contamination in the main multivariate analysis.

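### Start dates are drawn without regard to organ although heart, liver and lung have one department each, so chance can give the two periods a different kidney versus non-kidney mix

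*Protocol article*

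**What the plan says.** Study design and randomization lists seven departments: "four kidney transplantation units, one heart transplantation unit, one liver transplantation unit and one lung transplantation unit". The draw is described step by step. "The envelopes with department names and envelopes with start date will be prepared and shuffled by the researcher", and then "The independent professional then randomly chooses the envelopes". No stratification, pairing or acceptance rule is given.

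The same section fixes the start: "All seven participating departments commence the study with standard care i.e. the control period", in September 2020. It also gives one switch date: "The first department will be randomized to commence the experimental period in March 2021". Later dates are left to a figure ("For the schematic overview of the inclusion, see Fig. 1") that is not in the text available here. Trial status puts the expected end of inclusion in May 2022.

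Organ appears in the analysis in three ways:

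- The comparison that Data analysis labels primary is univariate and has no organ term: "Continuous outcomes at T1 between the patients in the control and experimental period will be compared and tested using the Mann-Whitney" test, or the t test.
- The linear mixed model in the same section has organ and transplant centre as covariates. Sample size refers to this mixed model as the primary analysis.
- Per-organ results are conditional and exploratory: "If the effect of the intervention is found to differ according to organ type then separate explorative multivariate analyses will be conducted".

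**The concern.** For heart, liver and lung the organ is the department. An early start gives a department few control and many experimental patients, and a late start does the reverse. An order that places kidney units mostly early or mostly late therefore gives the pooled control and experimental groups different organ mixes. With only seven units and one draw, such imbalance cannot be relied on to average out.

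Two results are exposed. The unadjusted T1 comparison would carry any kidney versus non-kidney difference in the outcome into the estimated effect. The exploratory per-organ estimate would rest on few experimental patients for a single-organ department that draws a late date. The plan itself treats organ as relevant: it is a covariate, a possible effect modifier and, in Strengths and limitations, part of the claim that the result would support use in all four groups.

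**Working it through.** **Inputs from the article.** Seven departments, four of them kidney. Inclusion runs from September 2020 to May 2022, 20 to 21 months. The first switch is at month 6. The target is 200 patients, 100 per group, and the planned effect is 0.38 SD.

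**Assumptions.** One department per step; equal spacing of 1, 1.5 or 2 months; steady accrual; 200/7 = 28.6 patients per department.

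**The plan's own figures.** At d = 0.38 and 80% power, the unadjusted size is 108.7 per group. Multiplying by (1 − 0.5²) gives 81.5, so 82 as stated, with an implied baseline correlation of 0.5 that the article does not give. The planned 100:100 split is what 1.5-month steps over 21 months produce; 2-month steps give 114:86.

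**Split within a department.** With start month s and window T, controls = 28.6 × s/T and experimental patients = 28.6 × (T − s)/T. The first department has 28.6 × 6/21 = 8.2 controls.

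**Organ-mix difference.** D = kidney share of the experimental group minus kidney share of the control group. Example of an extreme order (21 months, 1.5-month steps, kidney units on the first four dates):

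- Experimental: 20.4 + 18.4 + 16.3 + 14.3 = 69.4 of 100.
- Control: 8.2 + 10.2 + 12.2 + 14.3 = 44.9 of 100.
- D = 24.5 points.

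Over all 35 placements of four kidney units on seven dates (21-month / 20-month window):

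| Step | SD of D, points | Largest D, points | Draws with D over 10 points | Experimental patients, last department |
|---|---|---|---|---|
| 1 month | 7.9 / 8.2 | 16.7 / 17.3 | 23% | 12.2 / 11.4 |
| 1.5 months | 11.5 / 12.2 | 24.5 / 25.8 | 40% | 8.2 / 7.1 |
| 2 months | 15.7 / 16.8 | 33.3 / 35.7 | 63% | 4.1 / 2.9 |

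D averages zero over the draws.

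**Effect on the unadjusted comparison.** Shift = D × the kidney versus non-kidney difference at T1. The article gives no such difference; 0.3 SD is assumed.

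- One SD of the draw: 0.08 × 0.3 = 0.02 to 0.17 × 0.3 = 0.05 SD.
- Largest: 0.17 × 0.3 = 0.05 to 0.36 × 0.3 = 0.11 SD, or 13% to 28% of 0.38.
- At 1.5-month steps, one SD is 0.115 × 0.3 = 0.035 SD, or 9% of 0.38.

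**Single-organ departments.** One of the three takes the last date with probability 3/7 (43%). The per-organ standard error is √(1/n control + 1/n experimental) in SD units, over 21 months:

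- 1.5-month steps: √(1/20.4 + 1/8.2) = 0.41 on the last date, 0.37 on the middle date.
- 2-month steps: √(1/24.5 + 1/4.1) = 0.53 on the last date, 0.38 on the middle date.

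**Restricted draw.** The seven ranks sum to 28, so equal mean rank requires the four kidney ranks to sum to 16. With kidney units on ranks 1 and 7, the other two must sum to 8: {2, 6} or {3, 5}. That leaves 2 × 4! × 3! = 288 of 7! = 5,040 orders. Under even spacing D is zero in all of them, also when kidney units recruit twice as many patients. The thinnest single-organ cell rises from 4.1 to at least 6.8 (2-month steps) or from 8.2 to at least 10.2 (1.5-month steps), both over 21 months.

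**Information.** Within-department information is Σ n·p·(1 − p), with p the control share. It is unchanged if units are equal in size. With kidney units twice as large (36.4 against 18.2 patients), 2-month steps and 21 months, it is 41.7 on average without restriction. The two permitted patterns give 18.2 × 972/441 = 40.1 and 18.2 × 996/441 = 41.1, a mean of 40.6: a loss of just under 3%. With only the first-and-last rule it is 40.7, a loss of about 2%.

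**The case against.** The strongest reply is that the harm is confined. Data analysis calls the unadjusted comparison primary but also exploratory, Sample size gives the primary role to the mixed model, and the aims in the Introduction speak of controlling for medical characteristics. That model contains organ and centre, so an uneven organ mix is largely dealt with there. This stands. The protocol labels both analyses primary, however, so the unadjusted one cannot be set aside.

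A reader might infer more: that the draw can tie organ to period, or leave an organ almost without patients in one period. The text does not support that. Every department starts in control and recruits controls for at least six months, about 29% of its inclusion. On the experimental side, a cell of 3 to 4 patients needs 2-month steps, which the text does not give. The spacing that matches the planned 100:100 split leaves 7 to 8.

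It is also fair that chance imbalance is not bias in expectation, that the largest values above are extremes of 35 placements, that the 0.3 SD is assumed, and that per-organ estimates are imprecise under any draw (standard error about 0.37 SD at best). These points limit the size of the concern. They do not help a trial that makes a single draw of seven units. A fuller protocol may describe a restriction, but the article sets out its procedure in some detail and mentions none.

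**Conclusion.** The point holds as an avoidable weakness of the stated draw, not as a flaw that invalidates the trial. The kidney versus non-kidney mix can differ between periods by chance, with an SD of about 8 to 17 points and a maximum of about 17 to 36. This rests on even accrual, equal-sized units, one department per step and assumed spacing of 1 to 2 months; the actual dates would narrow the range. The imbalance bears on the unadjusted T1 comparison and is largely removed in the mixed model. Separately, a single-organ department on the last date may bring about 7 to 8 experimental patients (1.5-month steps) or 3 to 4 (2-month steps) to an exploratory analysis. Organ is not confounded outright with period, and no organ is nearly empty in the control period.

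**What to change.** Add one sentence to the envelope procedure: the first and last start dates are drawn among the four kidney units, the other five dates among the remaining departments, and the draw is accepted only if kidney and non-kidney units have the same mean start rank. This needs no extra patients, staff or data. The costs are fewer possible orders (288 instead of 5,040) and, if kidney units are twice as large as the others, about 2% to 3% less within-department information at 2-month steps.

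The article describes itself as a January 2021 version, and the first switch was planned for March 2021, so the dates may already be drawn. In that case, name the organ- and centre-adjusted mixed model as the basis for the conclusion, keep the unadjusted T1 comparison as descriptive, and report inclusion by organ and period so that readers can judge each per-organ estimate. A fixed minimum number of patients per cell is not needed.

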**Fig. 1 Fig1:**
[figure not shown]
Flowchart of the study

In the month prior to the initiation of the experimental period for each department, the NPs will be trained in the delivery of the intervention. At this point in time, there will still be patients in the control period who are yet to complete the follow-up measure. During this month they may receive care in the form of a standard consultation from this NP. Therefore, there is potential for ‘contamination’ of these control period patients in the sense that their NPs will have already received the training associated with the intervention. To limit the risk of contamination, the following strategies will be put in place: standard care protocol will be used in all consultations for control period patients, and the questionnaires will not be administered by the NP but will be sent out by the researcher.

The ZENN intervention will be conducted in the outpatient clinic of each participating department. Due to the COVID-19 pandemic, the possibility of carrying out the intervention through tele-medicine is being examined. For the schematic overview of the inclusion, see Fig. 1. To enhance the validity of the study, the Standard Protocol Items: Recommendations for Interventional Trials (SPIRIT) guidelines [33] will be followed.

### Eligibility criteria

#### Patients

Eligible patients are heart, kidney, liver or lung transplant recipients who have received a transplant in one of the participating centres. The NP will ask patients to participate and hand out the written information on the study. Inclusion criteria are: over 18 years old, between two and thirteen months elapsed after transplantation, sufficient command of the Dutch language and the presence of a functioning graft. Exclusion criteria are cognitive limitations, participating in other lifestyle or self-management promoting programmes which could influence the outcome, and in case of kidney transplant recipients, an expected need for renal replacement therapy within 3 months of inclusion.

#### Nurse practitioners

NPs that give post-transplantation care at the outpatient clinic and have not been trained in the ZENN intervention before will be included.

### The intervention

The ZENN intervention [22] is based on the theoretical framework of the self-regulation theory [34]. The main intervention strategies are based on evidence-based techniques, namely goal setting and pursuit, Solution-Focused Brief-Therapy [35, 36] and Motivational Interviewing [37]. In practice, this means that the intervention focuses on a positive approach in order to enhance patients’ intrinsic motivation and self-efficacy to encourage sustainable behaviour change.

The intervention is divided over several consultations, whereby the number of consultations depends on the logistical constraints of the setting and needs of the patient. In the initial session, a holistic review of how things are going in 14 life areas takes place, as outlined in the used communication aid, the Self-Management Web (see Fig. 2). The Self-Management Web is not a measurement tool, but is intended to structure the conversation, to open the view of both patient and NP to possible topics, and to make this visual for the patient. This web can also be revisited in subsequent sessions to make progress on personal goals visual and tangible. This tool is also suitable for patients who have lower health literacy or language skills [22].

**Fig. 2 Fig2:**
[figure not shown]
Self-management Web

After completing the Self-Management Web, the NP stimulates the patient to prioritize a life area and asks if he/she wants to address and set a SMART goal. A SMART goal is Specific, Measurable, Attainable, Relevant and Time-based. A global plan of action for goal attainment will be agreed upon. In addition, patients’ motivation for change and self-efficacy in relation to the goal will be discussed using visual analogue scales. The second and third session are used to evaluate the progress of goal attainment, facilitators and barriers are explored and if necessary, strengths emphasized and progress complimented, the action plan may be revised. In addition, motivation and self-efficacy will be evaluated and encouraged, alongside a discussion of internal versus external attribution of successes. This means that the patient will be stimulated to look at his/her own role in the success, to promote internal attribution of that success. The aim of the fourth session is to evaluate and discuss the goal attainment, relapse prevention and generalization of the learned skills to other situations. For a visual overview of the intervention see Fig. 3. The development of the ZENN intervention and its use has been extensively described elsewhere [22].

**Fig. 3 Fig3:**
[figure not shown]
Content of sessions 1–4 [22]

### Training

At the moment of transition to the experimental period, NPs will receive training in communication skills and intervention background by a psychologist ([name]). Both trainers were part of the team who developed the ZENN intervention. The content of the standardized training includes knowledge of the steps in the programme protocol, theoretical knowledge of behaviours change techniques, and practicing these techniques through role-play. NPs learn to activate patients to generate their own solutions rather than focusing on the problems and achieve progression towards personal goals in short space of time. The training consists of two blocks of three hours given on the same day. Due to the COVID-19 pandemic, the possibility of carrying out the training through e-learning and video conferencing is being examined. In addition, there is a booster session once implementation has begun with the aim of discussing cases and optimizing standardization between NPs. The experimental period starts immediately the day after the one-day training has been completed. An extensive description of the training according to the CRe-DEPTH criteria developed by Van Hecke et al. (2020) [38] can be found in Supplement A.

### Data collection and outcome measures

Patients who participate in the control or experimental period will be asked to complete online questionnaires at three points in time. Participants receive the questionnaires by email, or on paper, if requested. To promote completion of the follow-up during the control and experimental period, we will send participants two reminders if they have not completed the questionnaire.

#### Primary outcome measure—patients

The primary outcome measure is self-management skills, which will be assessed with the Skills and technique acquisition scale of the Health Education and Impact Questionnaire (heiQ) [39]. For an overview of the research questions and the used instruments, see Tables 1 and 2 in Appendix.

